### 2.9 Data collection

Data collection occurs digitally on the mobile application, in the online research environment of the National Centre for Transitional Medicine and Clinical Research—REDCap, and at specialist receptions in parallel. The volume of data collected varies from group to group and depends on the randomization. Participants in the digital group complete the tests on the mobile application and in the REDCap environment. Participants in the control group fill in the tests and the satisfaction questionnaire in the REDCap environment. Specialists fill in the satisfaction questionnaire in the REDCap environment.

In addition to the data from tests and databases, the following data will be collected:

1) frequency of headache days; 2) pain intensity; 3) medications used; 4) performance of tasks sent or set by the headache nurse; 5) performance of the tasks sent or set by a CBT therapist; 6) performance of the tasks sent or set by a physiotherapist.

During the research, several parameters will be measured. The longest time will be devoted to the patient’s completion of the tests at the beginning and end of the study—2–2.5h. The time required to complete the tests each week is between 5and 10 minutes. The methods used in the study are presented in more detail in Table 2. The testing data collected in all groups are presented in Table 3.

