### 2.2 Study design

This is a multi-centre, open-label, prospective, randomized, and controlled study on the interdisciplinary intervention of migraine with digital technology-mediated treatment options versus conventional treatment options.

In the preparation phase of the study, migraine patients and specialists from Estonia contributed to the project. They assessed the Migraine Buddy application [29] and found it to be overly difficult, especially during the aura and attack phases of a migraine. The data of the application must also be available to specialists and compatible with e-health.

While preparing and planning the study, it became clear that no interdisciplinary digital solution for the treatment of headaches currently exists. Existing solutions are mostly digital headache diaries with individual appendices. There is no solution that brings comprehensive treatment, including nurse counselling, psychotherapy, and physiotherapy, to the patient.

In 2020, Migrevention started developing an interdisciplinary mobile application and specialist dashboard for migraine patients. They conducted validation interviews with Estonian migraine patients before developing the digital solution. Validation interviews showed that patients are ready to implement digital education, CBT, and physiotherapy programs into their treatment plan. The development of the Migrevention application provided a good opportunity to study a digitally mediated interdisciplinary headache treatment and compare it with conventional treatment options. For this reason, we use the Migrevention application, which monitors the patient’s use of the system, andobtains information about patient preferences, their health behavior, the actual application of patients’ self-help skills, their need for clinical intervention, etc. The digital format allows for reminders and follow-ups on patients, enabling researchers or clinicians to monitor data in real-time. The importance of this has also been emphasized in previous studies [52]

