### 2.5 Primary outcome measure

The primary outcome measure is a reduction in the number of headache days (data derived from diaries) three months after the end of the interdisciplinary intervention programmes compared to the baseline (at the start of intervention).

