### 2.6 Secondary outcome measures

The secondary outcome measures are as follows: number of headache days six and nine months after finishing intervention (follow-up) (data derived from diaries); change in consumption of analgesics or triptans (data derived from diaries); change in pain intensity (data derived from diaries); changes in depression, anxiety scores (data derived from tests); increase in pain acceptance (data derived from tests); changes in quality of life (data derived from tests); changes in number of sick-leave days (data derived from the national e-health system); and assessment of impact on the burden of migraine through sick-leave days, disability rate, and specialist visits (data derived from e-health systems). Specific methods are presented in Table 1 and Table 2.

**Table 1 pdig.0000295.t001:** Methods used in the study.

Indicator	Method	Time	Procedures for use	Patient time for filling test	Investigator
Frequency of headaches	Digital diary, paper diary	Continuous	Continuous	> 2 minutes	Patient independently in the application or on paper
Medication use	Digital diary, paper diary	Continuous	Continuous	> 2 minutes	Patient independently in the application or on paper
Medication use	Prescription Centre	Continuously/Intervals ^1^	Continuously/Intervals ^1^	N/A	Specialist desktop/doctor or nurse.
The effect of headaches on everyday life	Headache Impact Test (HIT-6) [53]	Intervals ^1^	Intervals ^1^	2–5 minutes	The patient performs independently in the application or the test environment REDCap.
Screening for mental disorders	Emotional State Questionnaire (ESQ-2) [54]	Intervals ^1^	Intervals ^1^	2–5 minutes	The patient performs independently in the application or the test environment REDCap.
Mental disorders	Diagnostic and Statistical Manual of Mental Disorders, Fifth Edition (DSM-V) symptom checklist + Psychiatrist consultation (if DSM-V symptom checklist detects a mental health disorder	Intervals ^3^	Intervals ^3^	60 minutes	The patient performs independently in the application or the test environment REDCap and/or one psychiatrist appointment
Personality profile	Swedish Universities Scales of Personality (SSP) [55]	Once at the beginning of the study	Once at the beginning of the study	30 minutes	The patient performs independently in the the test environment REDCap.

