### 2.10 Interventions

NI conducted with the participants are detailed in Table 4. All materials sent to participants through the Migrevention Clinical solution (study group) or explained in a face-to-face appointment (control group) are based on the intervention manual and are the same in both groups. The discussion topics and materials are distributed in the order specified in the intervention manual. Since the study attempts to mimic a standard conventional intervention as closely as possible, in the case of conventional treatment (control group), the communication between the specialists and participants is not precisely described in the intervention manual, leaving each specialist free rein over communication.

**Table 4 pdig.0000295.t004:** Interventions by group.

	Study group (digitally mediated NI)	Control group (conventionally mediated NI)
Headache diary	Participant is filling DHD in the Migrevention Clinical mobile application.	Participant is filling PHD, usually used in conventional treatment.
Headache nurse counselling	The headache nurse sends self-help materials (previously recorded audio) to the participant through the Migrevention Clinical specialist dashboard and communicates with the patient through the chatroom connected to the Migrevention Clinical mobile application. The Participant receives notifications to the Migrevention Clinical mobile application about new tasks, listens to the materials, and if needed, asks the headache nurse additional questions via the chatroom. Communication through the chatroom is not limited.	The headache nurse arranges face-to-face meetings with the participant to provide conventional nurse counselling. Meetings take place only at agreed times.

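### Digital-arm participants may complete the self-reported secondary questionnaires in the treatment app while controls use only REDCap, and the split is not stated

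*Protocol article*

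**What the plan says.** Section 2.9 sets a collection rule for each arm. For the digital groups: "Participants in the digital group complete the tests on the mobile application and in the REDCap environment". For controls: "Participants in the control group fill in the tests and the satisfaction questionnaire in the REDCap environment".

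Table 1 (section 2.6) names a platform for each instrument. For HIT-6, ESQ-2, CPAQ-R, PASS, EUROHIS-QOL, HALT and HURT the entry is "The patient performs independently in the application or the test environment REDCap". For the personality profile (SSP), taken once at the start, it is REDCap alone: "The patient performs independently in the the test environment REDCap".

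The section 2.6 text draws several secondary outcomes from these tests, among them "changes in depression, anxiety scores (data derived from tests"), pain acceptance and quality of life. All three are worded as changes or increases.

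The app is also the treatment channel. Section 2.7 links it to the specialist's dashboard and gives rising depression or anxiety scores as an example of what may lead to a video consultation in the digital arms. Section 2.2 describes the digital format as allowing reminders and "enabling researchers or clinicians to monitor data in real-time".

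**The concern.** The trial is open-label and these outcomes are self-reported. A participant who answers in the app answers inside the product under evaluation, in a channel used by the treating specialist. A control answers in a research form, and the article describes no comparable visibility for it. If response behaviour or completeness depends on that setting, the difference begins after allocation. It would then be read as an effect of digital treatment.

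The Discussion aims to show that digital delivery is no worse than conventional delivery. A shift favouring the app could support that aim wrongly on the secondary outcomes, and a shift the other way could hide a benefit. Every arm already uses REDCap, so the difference is avoidable.

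**Working it through.** **1. The plan's own figure.** Section 2.3 gives 75 per group, and Table 3 gives eight groups: 8 × 75 = 600, the stated maximum. This point disputes no figure. Section 2.3 gives no effect size, SD or significance level.

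**2. Who can use which platform.** Reading section 2.9 with Table 1:

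| Instrument | Table 1 platform | Digital groups | Control groups |
|---|---|---|---|
| ESQ-2 (depression, anxiety) | app or REDCap | either; not stated which | REDCap |
| CPAQ-R (pain acceptance) | app or REDCap | either; not stated which | REDCap |
| EUROHIS-QOL (quality of life) | app or REDCap | either; not stated which | REDCap |
| PASS, HIT-6 | app or REDCap | either; not stated which | REDCap |
| SSP (baseline profile, not an outcome) | REDCap | REDCap | REDCap |

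Section 2.9 places controls in REDCap, so the app option in Table 1 can apply only to digital participants. The one instrument fixed to a common platform is not an outcome measure.

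**3. What survives in a change score.** Let b0 and b1 be the platform shift in the digital arm at baseline and at the later time point. Controls have none. The expected between-arm difference in change is then

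(true difference in change) + (b1 − b0).

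- Same platform at both times with a constant shift: b1 = b0, and the bias is zero.
- Baseline in REDCap and later values in the app: b0 = 0, and the whole of b1 survives.
- App at both times, but answering behaviour changes as the relationship with the specialist develops: b1 − b0 survives.

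The article does not fix the platform by time point, so none of these cases can be excluded.

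**4. Illustration of size.** The documents give no platform effect, so the values of s below are assumptions. Let s = b1 − b0, in units of the SD of the analysed change. Assume no true effect, a common SD, two-sided α = 0.05 and a normal approximation. For one study group against its paired control group, n = 75 per arm:

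SE = √(2/n) = √(2/75) = 0.163

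P(significant) = 1 − Φ(1.96 − s/SE) + Φ(−1.96 − s/SE)

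| Surviving shift s | s/SE | P(significant) |
|---|---|---|
| 0 | 0 | 5.0% |
| 0.05 SD | 0.31 | 6.1% |
| 0.10 SD | 0.61 | 9.4% |
| 0.20 SD | 1.22 | 23.2% |

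For scale, the difference detectable with 80% power at 75 v 75 is (1.960 + 0.842) × 0.163 = 0.457 SD under the same assumptions.

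**The case against.** The strongest reply is that the text does not establish how much is affected. Digital participants use REDCap as well as the app, so common REDCap values may already exist for some or all of these instruments. A platform list by instrument is also detail that an article may leave to the full protocol. The first part stands: a reader might infer that every questionnaire outcome is fully confounded with treatment, and the documents do not support that. The second part does not dispose of the point, because the article itself states a collection rule that differs by arm.

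Other parts of the reply also stand:

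- Both platforms are electronic self-completion without an interviewer. The difference is one of platform and context, which is narrower than paper against electronic.
- The outcomes are changes, so a constant shift cancels when the same platform is used throughout.
- Reminders are described only as something the digital format allows. They are not tied to questionnaires, and nothing says controls receive none. Real-time monitoring is likewise a stated capability, not a documented practice for each questionnaire.
- The video consultation is part of the digital package under test and is not itself measurement bias. Section 2.7 does not say that the scores prompting it are those entered in the app.
- Study group I has no nurse, CBT or physiotherapy component, so the idea of answering to one's therapist applies weakly there. Controls in groups II to IV also have therapists. The direction of any bias is open.
- The section 2.6 text does not name headache impact as a secondary outcome; HIT-6 appears only in the tables.

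A reader might also pool the four digital groups against the four control groups. At 300 v 300, a surviving 0.2 SD shift would give about 69% false positives. The arithmetic is right, but the article does not specify that comparison and section 2.8 sets out four paired settings, so the figure should not be attached to this plan.

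**Conclusion.** The point holds in a limited form. As written, section 2.9 and Table 1 let platform and visibility to the treating specialist differ by arm for self-reported secondary outcomes. Which instruments and time points are affected is not stated. Randomisation does not protect against such a difference.

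Its size and direction cannot be derived from the documents. The figures of about 9% and 23% depend on assumed shifts of 0.1 and 0.2 SD that arise or grow after baseline. They show sensitivity and do not estimate the bias.

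A reader might carry the point over to the main result. That would be wrong: "The primary outcome measure is a reduction in the number of headache days (data derived from diaries"), not from questionnaires. The diaries also differ by arm, but that is a separate matter. The change is worth making because it is cheap and closes a gap that analysis could not reliably close afterwards.

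**What to change.** Amend section 2.9 and Table 1 so that all eight groups complete every outcome questionnaire in REDCap, at baseline and at each later time point scheduled for that instrument, on the same schedule and with the same reminders. State that only these REDCap values enter the digital-versus-conventional comparison.

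Preferably, do not repeat the same instrument in the app at the same time point, because digital participants would then answer twice and controls once. If the sponsor keeps in-app scores for monitoring, label them as such and use them only to describe the digital groups.

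The cost is a wording change and the loss of in-app completion for the compared values. If in-app scores are kept, there is also some duplicate completion in the digital arms, on top of a battery that section 2.9 puts at 2–2.5 hours at the start and end of the study. No new system is needed, since digital participants already use REDCap.

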### 2.10 Interventions

NI conducted with the participants are detailed in Table 4. All materials sent to participants through the Migrevention Clinical solution (study group) or explained in a face-to-face appointment (control group) are based on the intervention manual and are the same in both groups. The discussion topics and materials are distributed in the order specified in the intervention manual. Since the study attempts to mimic a standard conventional intervention as closely as possible, in the case of conventional treatment (control group), the communication between the specialists and participants is not precisely described in the intervention manual, leaving each specialist free rein over communication.

**Table 4 pdig.0000295.t004:** Interventions by group.

	Study group (digitally mediated NI)	Control group (conventionally mediated NI)
Headache diary	Participant is filling DHD in the Migrevention Clinical mobile application.	Participant is filling PHD, usually used in conventional treatment.
Headache nurse counselling	The headache nurse sends self-help materials (previously recorded audio) to the participant through the Migrevention Clinical specialist dashboard and communicates with the patient through the chatroom connected to the Migrevention Clinical mobile application. The Participant receives notifications to the Migrevention Clinical mobile application about new tasks, listens to the materials, and if needed, asks the headache nurse additional questions via the chatroom. Communication through the chatroom is not limited.	The headache nurse arranges face-to-face meetings with the participant to provide conventional nurse counselling. Meetings take place only at agreed times.
Cognitive-behavioral therapy	The clinical psychologist sends CBT based self-help materials (previously recorded audio), diaries (previously built-in) and exercises (previously recorded audio), through the Migrevention Clinical specialist dashboard. The Participant listens to audio materials and fulfils diaries inside the Migrevention Clinical mobile application. The clinical psychologist gives written feedback for the participant after they have filled their diaries. A possibility to give feedback to the patient is built-in to the Migrevention Clinical specialist dashboard. It is also possible for the participant to start a chatroom with the clinical psychologist if needed. Communication through the chatroom is not limited.	The clinical psychologist arranges face-to-face meetings with the participant to provide conventional CBT. Meetings take place only at agreed times.
Physiotherapy	The physiotherapist sends self-help materials (previously recorded audio) and exercises (previously recorded video) through the Migrevention Clinical specialist dashboard. The Participant listens to audio materials and performs the assigned exercises according to the videos inside the Migrevention Clinical mobile application. The physiotherapist can give written feedback for the participant after their tasks are done. A possibility to give feedback to the patient is built-in to the Migrevention Clinical specialist dashboard. It is also possible for the participant to start a chatroom with the physiotherapist if needed. Communication through the chatroom is not limited.	The physiotherapist arranges face-to-face meetings with the participant to provide conventional physiotherapy. Meetings take place only at agreed times.

### 2.11 Statistical analysis

The programs SPSS and R will be used for data analysis. The use of the main generalized linear models for data analysis, such as ANOVA, MANOVA and multinomial linear regression analysis, is planned.

### 2.12 Ethics and approvals

All patients wishing to participate in the study will be given a written informed consent form to read during their first appointment with their neurologist. Patients have the right to refuse to participate in the study, to suspend their participation in the study, and to prohibit the use of their data in the study at any time.

On the digital platform and in the REDCap online environment, the data are collected in a personalized form. After the end of the personal intervention and the data quality control, personal data are separated from survey data. The data will be exported from the research server (server of the National Centre for Transitional Medicine and Clinical Research, Quretec server) to a computer for data processing (Microsoft Office Excel). All data are analyzed in confidence with personal users and only for the purposes of this research under the Personal Data Protection Act [[61]. The data are stored in digital form on the server of the National Centre for Transitional Medicine and Clinical Research (REDCap online environment) and the server of Quretec OÜ (digital platform). For data processing, the data are downloaded to the computer (Microsoft Office Excel) in encrypted form. The code key will be in a folder encrypted by the responsible researcher in the Neurology Department of Tartu University Hospital, and only the responsible researcher has access to it. The planned retention period of the data and the code key is 30 years (until 12/2050), which will allow for longitudinal studies, follow-up analysis, and data quality control of the topic in the future, when necessary.

#### Potential risks associated with the study

In this study, the participants are asked to complete questionnaires, some of which are not routinely used in the clinical assessment of this group of patients, thus placing a somewhat greater time burden on the study participants than on regular patients. No patients will be deprived of their medication during the study, their medication will not be affected in any way, and there will be no additional risks for the participants.

## 3. Discussion

Designed by an interdisciplinary team, our research aims to compare digitally mediated NI migraine treatment options with conventional ones, determine the optimal approach for enhancing patient health and quality of life, optimizing specialists’ time, and extending assistance to more migraine patients.

A notable strength of this study is its status as a prospective randomized controlled study of a novel, standardized, manual-based intervention that focuses on, among other things, monitoring compliance and compares fully digital intervention with conventional interdisciplinary NI. Another strength of the study is the assessment of the efficacy and applicability of each treatment component separately, in addition to the whole treatment protocol.

The authors hope that the study helps to overcome the challenges in the field of digital therapeutics (DTx) [62]. The study provides an opportunity to begin to determine the effectiveness of DTx in the treatment of migraine. The implementation of the project also contributes to the integration of DHD data with the e-health system so that they are usable for all providers (including general practitioners) as well as the connection of DHDs to electronic health records.

Interdisciplinary intervention in migraine treatment is known to be effective, especially in preventing migraine chronification [63]. Given the high risk of migraine chronification, long-term treatment adherence and follow-up may be essential to ensure the long-term effectiveness of digital interventions [64]. Based on the above, the research plans to conduct long-term follow-up studies (3, 6, 9 months after the end of the intervention).

There are some limitations that may affect the conduct and results of the study and must be considered when interpreting the results in the future.

The initial sample size will see at least 75 patients in each group, according to the Power analysis. Due to the time-consuming conventional interventions and the time needed to collect data, the realistic obtainable group size within the given timeframes of the study may be smaller. The study may favour the larger clinics and research centers for adopting the protocol and conducting the study and limit similar possibilities of smaller centers. In order to overcome this problem, interim analyses can be undertaken to examine statistically significant associations in a smaller number of patients.

Digital interventions, which are not conducted via video call, are unique strategies that may not be the preference of many individuals in certain situations. In digital interventions, the authors have planned patient initiated clinical contact only via chatroom. Studies on whether and how much clinical contact is required are controversial [14, 65]. The lack of human connection may affect patient adherence, increase the drop-out rate and limit treatment efficacy for some patients. The predetermined and limited number of techniques for use by the specialists may affect the flexibility of treatment. It must also be considered that the entire intervention programme is a minimum programme, and minimal intervention may not have sufficient power to prove the effectiveness of NI migraine treatment.

The whole intervention being done on Estonian patients is a limitation by itself. Estonia is a digitally advanced country whose residents use digital solutions daily. These settings may not be equivalent in other countries and cultures. Hence, the developed methodology is best applicable in countries with similar settings and consequently must be repeated in other countries with different settings.

The authors intend to demonstrate that digitally mediated treatment is at least as effective as conventional treatment but allows for a significantly higher patient throughput, saves/improves specialist workload and is cost-effective. The authors expect remote monitoring and high-quality digitally mediated interventions to be the future of chronic disease treatment.

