Limited studies have explored virtually mediated nurse counselling and digital physiotherapy. While a virtual nurse (avatar) may address healthcare challenges, it cannot diagnose or collaborate with other team members [40]. Online chatroom counselling with nurses offers opportunities to enhance clinical contact in digitally mediated interventions, but various limitations and challenges need addressing [49]. To our knowledge, the efficacy of digital physiotherapy in interdisciplinary headache treatments remains unstudied. A global shortage of headache specialists, including clinical psychologists, CBT therapists, physiotherapists, and headache nurses, contributes to long waiting lists and limited availability. Geographic constraints further impede access to services, particularly for those residing far from large centers. Digital NI options address these challenges by expanding access to services, utilizing professional intervention methods, reducing dropout rates, and thereby improving intervention efficacy [50,51].

The main goal of the present study is to assess the efficacy of interdisciplinary digital interventions compared to conventional treatment options.

The essential secondary objectives encompass evaluating individual and combined components of interventions, including adherence, credibility, clinical contact, and cost-effectiveness in comparison to conventional format.

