### 2.8 Settings and randomization process

The study will be conducted in parallel for each intervention setting—the four study groups (digital treatment groups) and the four control groups (standard interdisciplinary treatment groups or treatment standard groups) (Table 3).

**Table 3 pdig.0000295.t003:** Division of groups.

Study group I	Control group I	Study group II	Control group II	Study group III	Control group III	Study group IV	Control group IV
UMT^1^	UMT	UMT	UMT	UMT	UMT	UMT	UMT
DHD^2^	PD^3^	DHD	PD	DHD	PD	DHD	PD
		DHN^4^	UHN^5^	DHN	UHN	DHN	UHN
				dCBT^6^	uCBT^7^	dCBT	uCBT
						dPT	uPT

^1^UMT–Usual Minimal Treatment

^2^DHD–Digital Headache Diary

^3^PD–Paper Diary

^4^DHN–Digital Treatment by Headache Nurse

^5^UHN–Usual Treatment by Headache Nurse

^6^dCBT–Digital CBT Programme

^7^uCBT–Usual CBT Programme

^8^dPT—Digital Physiotherapy

^9^uPT–Usual Physiotherapy

After the initial informed consent, patients who qualify for the study will be added to the research group and assigned a participation number based on the precise time the study group acquired the contact information of the patient (date and time, if necessary). After the informed consent is signed, participants are randomized into eight groups. A randomization table has been created for this purpose, in which 600 distinct numbers are randomly separated into eight groups. The patient is assigned to a group in accordance with the randomization table.

All groups receive the usual minimal treatment consisting of medications in addition to the usual appointment with a neurologist. Control groups receive the usual treatment consisting of medications, the usual appointment with a neurologist, headache nurse, CBT therapist and a physiotherapist, in different combinations. All ‘as usual’ treatments involve clinical face-to-face contact.

All participants of the study groups receive digital treatment consisting of medications and a neurologist appointment as usual. Additionally, each participant is assigned digital appointments with the following specialists: headache nurse, CBT therapist and/or physiotherapist. These appointments are assigned in different combinations depending on the randomization. The digital interventions are delivered through the Migrevention Clinical solution.

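### The nested groups estimate the added effect of CBT and of physiotherapy on top of the earlier components, not the separate efficacy that the article claims

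*Protocol article*

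**What the plan says.** The Discussion (section 3) lists as a strength the "assessment of the efficacy and applicability of each treatment component separately, in addition to the whole treatment protocol". Section 1 (Background) gives as an essential secondary objective "evaluating individual and combined components of interventions, including adherence, credibility, clinical contact, and cost-effectiveness in comparison to conventional format".

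Section 2.8 and Table 3 define eight groups, four digital (study) and four conventional (control). All receive usual minimal treatment and keep a diary. Group II adds the headache nurse, group III adds CBT to that, and group IV adds physiotherapy to that. The text describes the control groups as seeing a "headache nurse, CBT therapist and a physiotherapist, in different combinations", and says of the digital appointments: "These appointments are assigned in different combinations depending on the randomization". Allocation uses a table "in which 600 distinct numbers are randomly separated into eight groups". Section 2.3 plans 75 patients per group and 80% power.

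**The concern.** A claim to assess the efficacy of each component separately leads a reader to expect an answer to whether CBT helps, or whether physiotherapy helps, as a component in its own right. Table 3 has no group that receives CBT without the nurse, and none that receives physiotherapy without nurse and CBT. A service able to offer only one of these would find no group matching its situation.

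The same structure affects the comparison of formats. From level II upwards, the study and control groups at a given level differ in the format of every component they receive, so that comparison does not isolate the format of the component added last.

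At stake is what may be concluded about CBT and physiotherapy. If group IV does no better than group III, the finding is that no added benefit of physiotherapy was detected in patients who also receive the nurse and CBT. It says nothing about physiotherapy without them.

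**Working it through.** **Inputs.** Group contents: Table 3, section 2.8. Group size 75, 80% power, maximum 600: section 2.3. The article gives no alpha, sidedness, effect size or SD for the power analysis. Two-sided alpha of 5% and results in SD units are assumed here.

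**Plan's own figure.** 8 × 75 = 600, as stated. The 75 per group cannot be reproduced without the missing inputs.

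**Step 1: group contents, the same pattern in each format.**

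| Level | Diary | Nurse | CBT | Physiotherapy |
|---|---|---|---|---|
| I | yes | – | – | – |
| II | yes | yes | – | – |
| III | yes | yes | yes | – |
| IV | yes | yes | yes | yes |

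**Step 2: what the group means identify.** Take usual treatment plus diary as the base m. Let N, C and P be the effects of nurse, CBT and physiotherapy, each added alone to that base, and let products denote interactions. Within a format:

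- I = m
- II = m + N
- III = m + N + C + NC
- IV = m + N + C + P + NC + NP + CP + NCP

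Hence:

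- II − I = N
- III − II = C + NC
- IV − III = P + NP + CP + NCP

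The nurse effect over usual treatment plus diary is isolated. C and P are not, because each comes bundled with its interactions. A rank check agrees: a full model for four components, diary included, has 2⁴ = 16 parameters, and four cells give rank 4. If all interactions are set to zero, the model has four parameters and rank 4, so C and P become estimable. But the four cells are then used up and leave nothing to test that assumption.

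**Step 3: format comparisons.** Study I versus control I differs only in the diary, so diary format is isolated. Study III versus control III differs in the formats of diary, nurse and CBT together. The format effect at the CBT step is

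(study III − study II) − (control III − control II),

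and similarly for the nurse and physiotherapy steps.

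**Step 4: precision.** Detectable difference = (1.960 + 0.842) × √V = 2.802 × √V, with V the variance of the contrast in SD² units.

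| Contrast | V | Detectable at 80% power |
|---|---|---|
| One increment within a format, or study vs control at one level (75 vs 75) | 2/75 | 2.802 × 0.163 = 0.46 SD |
| One increment pooled over format (150 vs 150) | 2/150 | 2.802 × 0.115 = 0.32 SD |
| Format effect of an added component (four groups of 75) | 4/75 | 2.802 × 0.231 = 0.65 SD |

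At a true difference of 0.458 SD, the size for which 75 versus 75 gives 80% power, the last contrast has power Φ(0.458/0.231 − 1.960) = Φ(0.02), about 51%.

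**The case against.** The strongest reply is that a cumulative add-on design is legitimate, and that assessing components separately can be read as decomposing the full programme step by step. Table 3 delivers that: all three increments are randomized contrasts, and they equal the separate effects if the components do not interact. This stands as a defence of the design. It does not rescue the wording, which sets each component apart from the whole and never mentions increments or additivity.

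A second reply is that contrasts belong in an analysis plan that is not shown. That is right for how contrasts are specified. But the point concerns a claim the article makes, and no analysis plan can supply groups that were not randomized.

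Several stronger readings are tempting, and the document does not support them:

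- *No component can be isolated.* II versus I isolates the nurse over usual treatment plus diary, and study I versus control I isolates diary format.
- *The whole secondary objective fails.* It also covers adherence and other aspects, and the Discussion claim also covers applicability. Section 2.9 records task performance separately for nurse, CBT therapist and physiotherapist, so these can be described by component.
- *Components are confounded with order of delivery.* Table 3 shows what each group receives, not the sequence in time.
- *Section 2.8 is wrong to speak of different combinations.* Nurse; nurse plus CBT; and nurse plus CBT plus physiotherapy are different combinations.
- *The investigators will read a null IV versus III result as physiotherapy not working.* Nothing in the article says so. The present wording merely leaves that reading open.

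**Conclusion.** The point holds for efficacy. For CBT and physiotherapy, two of the three specialist components, the design gives the effect of adding the component to all earlier ones. Stand-alone efficacy follows only under a no-interaction assumption that is unstated and untestable in these groups. This rests on Table 3 alone and needs no numerical assumption.

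For the format effect of an added component, the relevant contrast has twice the variance of a pairwise comparison, so its detectable difference is √2 times larger: about 0.65 SD against 0.46 SD. These figures assume two-sided 5% alpha, full groups of 75, equal SDs and no adjustment for multiple comparisons. The 0.32 SD for a pooled increment describes an average over formats, and serves as a single answer only if the increment is similar in both.

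The main goal, digital against conventional programmes, is not affected.

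**What to change.** 1. In section 3, and for component efficacy in section 1, replace the claim of separate assessment with three incremental effects: nurse added to usual treatment plus diary (II − I), CBT added to diary plus nurse (III − II), and physiotherapy added to diary plus nurse plus CBT (IV − III).
2. State there that stand-alone efficacy of CBT and of physiotherapy cannot be concluded from this trial.
3. Since the secondary objective is framed against the conventional format, name the format-by-level difference of differences as the contrast for the digital-versus-conventional effect of an added component. Acknowledge its lower precision. Describe study versus control at levels II to IV as a comparison of package formats.

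The statements on adherence and applicability by component can stay, as can section 2.8, the eight groups and the sample size. The cost is a few sentences and a narrower claim.
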